#### Patient withdrawal

Study participants may leave the study at any time and may withdraw consent to study participation without negative consequences. The reasons for discontinuation will be asked in the consent form and will be recorded.

### Interventions

#### Explanation for the choice of comparators {6b}

The WHO low-intensity psychosocial intervention “healthy thinking” is to be provided through platform VSee. The comparative arm is selected from the same setting to prevent any selection bias.

#### Intervention description {11a}

##### Intervention group (IG)

This a series of Low-Intensity Psychological Interventions based on the healthy thinking manual. The Thinking Healthy approach attends to giving attention to overall maternal mental well-being by delivering a simplified form of cognitive behavior therapy (CBT) recommended by the Mental Health Gap Action Programme (mhGAP) [19]. It will be tailored and delivered through six video conferencing sessions, real-time interaction between patients and therapists via VSee video connection. Each session is a one-to-one session and may last up to 45 min. Adherence will be monitored and documented on logbooks and medical records. Details about the sessions are available in the WHO manual.

##### Control group (CG)

Participants in the CG will be screened for outcomes via the same platform in addition to usual care.

#### Criteria for discontinuing or modifying allocated interventions {11b}

Participants can leave the study at any time and may withdraw consent. There will be no criteria for discontinuing or modifying allocated interventions.

#### Strategies to improve adherence to interventions {11c}

The data collectors will ensure the participants’ adherence in both groups through phone reminders about their appointment and the flexible, convenient booking of their meetings.

#### Relevant concomitant care permitted or prohibited during the trial {11d}

In severe depression or suicidal ideation during the study, the participant will be referred to urgent psychiatric care based on HMC Guidelines and receive appropriate treatment.

#### Provisions for post-trial care {30}

There is no anticipated harm, and investigators will not provide compensation for trial participation. The participants identified in the trial suffering from maternal mental distress will be receiving care, follow-up, and treatment from psychiatry based on HMC Guidelines.

### Participant timeline {13}

Prospectively, the participants will be followed for approximately 1 year (from their second trimester to around 8 to 10 months postnatal). Participants will be enrolled and assessed following the Standard Protocol Items: Recommendations for Intervention Trials (SPIRIT) schedule as shown in Table 1.

**Table 1 Tab1:** SPIRIT schedule

	Study period						
	Screening	Allocation	Post-allocation				
	Pregnancy		Pregnancy		Postpartum		
Timepoint**	***T-***_***1***_	**0**	***T***_***0***_	***T***_***1***_	***T2***	***T3***	***T5***
Eligibility screen	X						
Informed consent	X		X	X	X	X	X
Randomization		X					
Interventions:							
				X	X	X	X
Telemental low-intensity psychosocial interventions A							
Control Group B				X	X	X	X
Assessments:							
1. Mental health history	X						
2. Medication use	X						
3. COVID-19 status			X	X	X	X	X
4. Perinatal depression			X	X	X	X	X
5. COVID-19-specific phobia			X	X	X	X	X
6. Perinatal anxiety			X	X	X	X	X
7. Sociodemographic characteristics			X	X	X	X	X
8. Pregnancy-related factors			X	X			
9. Acute medical problem			X	X	X	X	X
10. Previous maternal and neonatal complication			X	X			
11. Chronic illnesses			X	X			
12. Behavioral factors			X	X	X	X	X
13. Stressful life events			X	X	X	X	X
14. Newborn health					X	X	X

*T*_*−1*_ before enrolment it is the screening phase in the 2nd trimester [14th week until the end of 27th], *T*_*0*_ after randomization and allocation it is baseline assessment [14th week until the end of 27th], *T*_*1*_ is during the 3rd trimester [28th week until the end of 42nd week] the first intervention session, *T*_*2*_ during early postpartum 3–5 weeks, *T*_*3*_ in 2–4 months postpartum, *T*_*4*_ in 5 to 7 months postnatal, *T*_*5*_ in 8 to 10 months postnatal

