#### Phase two: screening and enrolling participants

The investigators will follow the Consolidated Standards of Reporting Trials (CONSORT) in displaying steps of recruitments and randomization. The eligible participants will be selected randomly from the registered pregnant women at Women Wellness and Research Centre (WWRC) and will be contacted by phone to inform the study through verbal informed consent.

Randomization (1:1) with an automated online system ensuring that the research team will not affect randomization. Participants will complete all the assessments via telephone interviewing but following a prewet transcript, and therefore, their responses could be affected by the trial team. A cohort of participants will be followed from the time of approval of the study until the end of interventional sessions (T5-session 6), approximately 1 year after the baby is born. Figure 1 summarizes the study flow.

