#### Who will take informed consent? {26a}

The consent will be taken by delegates’ obstetrics and gynecology physicians of the approved representatives from WWRC in the screening phase through the phone. In the data collection phase, the psychologists will take consent at the beginning of the video call prior to the interview.

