#### Concealment mechanism {16b}

Random allocation of the participants will be done into the intervention and control groups. Concealment of group allocation will be done to minimize selection bias. Before commencing the first session, one investigator will randomly allocate eligible participants into two groups. Each participant’s contact details will be written on a printed paper and sealed in an envelope marked with either letter A or B.

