#### Implementation {16c}

At the implementation level, another investigator will follow-up with the sessions. The investigator will also hand equal numbers of envelopes to each psychologist randomly. Each psychologist will then open the envelope and contact the patient to begin the teleconsultation session. Patients will give their consent verbally over the phone prior to any teleconsultation sessions.

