### Statistical methods

#### Statistical methods for primary and secondary outcomes {20a}

Quantitative variables will be described as mean and standard deviations, whereas the frequency with percentages will be calculated for categorical variables. Both the intervention group and control groups will be described in a table with all the characteristics. Chi-square test will be applied to compare percentages of categorical variables. Regression analysis will be carried to stratify data to eliminate potential confounders and effect modifiers. P value 0.05 (two-tailed) was considered for statically significant level.

We will analyze each continuous outcome with a linear mixed-effects regression model to account for the repeated measures over time. We will analyze binary outcomes with a logistic mixed-effects model. Mixed-effects models are the recommended statistical technique for analyzing clinical trials when outcomes are collected at repeated time points. This trial included outcome data at gestation weeks 14 to 40, 3 to 5 weeks postnatal, 2 to 4 months postpartum, 5 to 7 months, and 8 to 10 months postpartum or postnatal available for all participants who will be randomly assigned. The logistic mixed-effects model has the advantage of implicitly accounting for data missing at random. The estimated (adjusted) effect differences from these analyses therefore will be reported. The linear mixed-effects models will include the response variable, timepoint, randomized group, and baseline score as fixed effects. We will model an interaction between time and the randomized group as a fixed effect to estimate treatment effect at all timepoints. Gestational age and postpartum weeks will be included as covariates in the model. We will calculate standardized effect sizes with Cohen’s d.

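### Baseline (T0) scores are scheduled after allocation with unblinded interviewers, yet serve as the model's baseline covariate and the anchor of the T1–T0 change

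*Protocol article*

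**What the plan says.** **Order of steps.** In the protocol article, Participant timeline {13}, Table 1 runs from Screening to Allocation to a Post-allocation block whose first column is T0. The footnote agrees: T0 is "after randomization and allocation it is baseline assessment [14th week until the end of 27th" week. The three outcome scales are marked from T0 onward and not at screening.

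**Who allocates and who interviews.** Concealment mechanism {16b}: "Before commencing the first session, one investigator will randomly allocate eligible participants into two groups". The contact details go into a sealed envelope bearing the letter A or B, and Table 1 uses A for the intervention and B for control. Implementation {16c}: "Each psychologist will then open the envelope and contact the patient to begin the teleconsultation session". The retention section {18b} has psychologists collecting the data by interview. Section {17a} blinds only the data analyst and data entry. The Phase two section concedes that the trial team may influence the women's answers.

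**Consent.** It is obtained by phone at screening, and again at each later contact: "In the data collection phase, the psychologists will take consent at the beginning of the video call prior to the interview".

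**Use of T0.** Section {20a}: "The linear mixed-effects models will include the response variable, timepoint, randomized group, and baseline score as fixed effects". The same model has a time-by-group interaction, to estimate the effect at every timepoint. Outcomes {12} defines changes between successive visits, the first being T1–T0.

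**The concern.** A baseline covariate is safe to adjust for because allocation cannot have influenced it. Here allocation comes first, and the score is obtained by interview from someone who probably knows the arm. Expectation on the woman's side, if she has been told her arm, or the interviewer's manner, could move the T0 scores differently in the two arms. The model would then adjust for a variable that carries part of the allocation's effect, and the T1–T0 change would start from a displaced point. T1–T0 matters because the Abstract places the primary endpoint in the third trimester, which is T1.

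There is also a gap between allocation and the first score. A woman who declines at the T0 consent has been randomised but contributes no outcome data at all, and her refusal may depend on her arm. Since no score is taken at screening, nothing earlier can replace a compromised or missing T0.

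**Working it through.** **1. The plan's own figure.** Statistical methods {14} gives 29 per arm for 34% versus 70%, two-sided alpha 0.05, power 80%, ratio 1. With pooled variance under the null and mean proportion 0.52:

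n = [1.960 × √(2 × 0.52 × 0.48) + 0.842 × √(0.34 × 0.66 + 0.70 × 0.30)]² / 0.36² = 29.03,

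which reproduces 29 (power at 29 is 79.96%). The unpooled formula printed in the article gives 26.3. That is a separate matter, and this point does not depend on it. The 29 is used below only as the arm size.

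**2. Does the interviewer know the arm at T0?** Allocation precedes the first session, the letter is on the envelope, the psychologist opens it before making contact, and no other T0 assessor is named. Together these make knowledge of the arm at T0 likely. No sentence states it.

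**3. Bias from a shifted T0.** Assume unit SDs, correlation rho between T0 and follow-up, no true effect, and a T0 shift of b SD in the intervention arm with follow-up undistorted.

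- Change score: bias = 0 − b = −b.
- Baseline-adjusted: bias = 0 − rho × b = −rho × b.

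On a scale where higher is worse, as stated for the phobia scale, an upward shift at T0 in the intervention arm flatters the intervention. A downward shift does the reverse.

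**4. Simulation.** 29 per arm, one outcome, one follow-up visit, 4,000 replicates, two-sided 5% test. Both b and rho are assumed; the documents give neither. Each cell shows rho = 0.5 / rho = 0.7.

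| b (SD) | Bias, change | Type I error, change | Bias, adjusted | Type I error, adjusted |
|---|---|---|---|---|
| 0 | 0.00 / 0.00 | 4.8% / 5.3% | 0.00 / 0.00 | 5.1% / 5.5% |
| 0.1 | −0.11 / −0.11 | 6.8% / 7.3% | −0.05 / −0.08 | 5.6% / 6.3% |
| 0.2 | −0.21 / −0.20 | 12.2% / 16.2% | −0.11 / −0.14 | 7.5% / 11.5% |
| 0.3 | −0.30 / −0.30 | 19.4% / 30.8% | −0.15 / −0.21 | 9.1% / 18.8% |
| 0.5 | −0.49 / −0.50 | 44.7% / 67.4% | −0.24 / −0.35 | 17.2% / 41.9% |

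The simulated biases agree with the formulas within simulation error. The b = 0 row is the case of T0 taken before allocation.

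**5. If the distortion persists.** Let a fraction k of the shift also affect the follow-up score. The biases become −(1 − k) × b for the change and (k − rho) × b for the adjusted effect. At k = 1 and b = 0.2 the change is unbiased, and the adjusted effect is off by 0.2 × 0.5 = 0.10 (rho 0.5) or 0.2 × 0.3 = 0.06 (rho 0.7), with the opposite sign. So without k, neither the size nor the sign of the net bias can be known.

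**6. Refusal at T0.** Each such woman is 1/58 = 1.7% of the trial, or 1/29 = 3.4% of her arm, with no score at any visit.

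**7. Is T0 before treatment?** The footnote says T1 "is during the 3rd trimester [28th week until the end of 42nd week] the first intervention session", and Table 1 marks no intervention at T0. But the Phase two section follows women "until the end of interventional sessions (T5-session 6"), and the intervention is "delivered through six video conferencing sessions". T1 to T5 is five timepoints; T0 to T5 is six. At one session per timepoint, T0 would be session 1, against the footnote. The documents do not say that there is one session per timepoint, so the passages need to be reconciled.

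**The case against.** The strongest reply is that T0 is still untreated: Table 1 starts the intervention at T1, and the items are fixed scale questions read from a script. On that reading only knowledge of the arm can act on T0, and nothing shows that it did. This stands as a limit on size. It does not make T0 a pre-randomisation measure.

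Four stronger readings are tempting, and the documents do not support them.

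- **That women are allocated before they consent to the trial.** They are not. Sections {26a} and {16a} and Table 1 put consent at screening, before randomisation. The consent at T0 is one of a series repeated at each contact. Withdrawal after randomisation is possible under any order of steps; what remains is that here it can happen before any score exists.
- **That women without T0 are dropped from the analysis.** Section {20c} states intention to treat and plans multiple imputation, with details left to the analysis plan. For these women an imputation would have no outcome data of their own to draw on, but exclusion is not stated.
- **That the psychologist has certainly opened the envelope at T0, and that the woman knows her arm.** Section {16c} ties the opening to the teleconsultation session. Section {16a} describes a coded list with phone numbers, and {18a} has psychologists phoning to book interviews, so contact without the envelope is conceivable. No text says that the woman is told her arm before T0.
- **That all change scores rest on T0.** Only T1–T0 does; the others run between successive later visits. The baseline covariate, in contrast, enters the estimate at every timepoint.

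A further fair point is that the same unblinded psychologists collect the later scores, so a lasting distortion could partly cancel. The plan cannot rely on two unknown distortions being equal. Equally, moving T0 does not cure any distortion of the follow-up interviews, which is a separate matter.

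**Conclusion.** The point holds in this form: the document itself schedules the baseline outcome scores after allocation, has no earlier score, leaves the interviewers unblinded, and uses T0 both as a covariate at all timepoints and as the anchor of T1–T0. That the interviewer knows the arm at T0 is a strong inference from the envelope procedure, not a stated fact.

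The size of any bias cannot be derived from the documents. The table above is an illustration that rests on an assumed shift, an assumed correlation and distortion confined to T0. A reader might infer from it that the trial's result will be biased by a given amount, or that treatment itself has already acted on T0. Neither follows. What does follow is that the plan gives up, for no stated reason, the protection that a pre-allocation baseline provides, and that analysis cannot restore it once enrolment has begun. The Trial status section says that recruitment had not started. Figure 1 (study flow) was not available for this check; if it shows T0 before allocation, it contradicts Table 1 and the same correction is needed.

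**What to change.** 1. Keep the screening consent as it is. Then take T0, then randomise, then release the arm. If randomisation must come earlier, at least withhold the arm from the psychologist and the woman until T0 is complete.
2. In Table 1, move the T0 column ahead of Allocation. Reword the footnote to say, for example, that T0 is the baseline assessment in weeks 14 to 27, after screening consent and before randomisation.
3. In Concealment mechanism {16b} and Implementation {16c}, state that the marked envelopes are handed over and opened only after the T0 scores are recorded. The coded phone list in {16a} can serve to arrange the T0 interview.
4. Reconcile the session numbering in the Phase two section and the count of six sessions with the footnote on T1, so that it is clear whether any session coincides with T0.

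The cost is wording and a change in the order of planned steps within the same 14–27 week window, with no added contact for participants. Women who decline at T0 would no longer be randomised, so a few more may have to be screened to reach 58.

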### Outcomes {12}

#### Primary outcomes

The primary outcomes are baseline (T0) scores of perinatal depression, perinatal anxiety, and COVID-19-specific phobia during late pregnancy and during the follow-up up to 10 months postpartum, additionally computing the changes in the scores from the baseline [(T1–T0), (T2–T1), (T3–T2), (T4–T3), and (T5–T4)].

We will evaluate the primary outcomes through video conferencing sessions via VSee video connection based on standard tools.

Edinburgh Postnatal Depression (EPDS-10) will be used to assess perinatal depression. The scale showed to be a reliable screening tool in Qatar [9]. Cumulative evidence demonstrated a pooled sensitivity of 0.80 and a pooled specificity of 0.81 [21].

The anxiety subscale of EPDS-3A will be used to assess perinatal anxiety. It is identified to have acceptable sensitivity and specificity based on a systematic review of perinatal anxiety tools [22].

Corona-specific phobia, a severe fear specific to the emerging virus, will be assessed through the Corona-Specific Phobia questionnaire that consists of a seven-item scale. Answers are based on the five-item Likert-type scale, and it showed internal consistency (*α* = 0.82) with robust psychometric properties. A total score is calculated by adding up each item score (ranging from 7 to 35). The higher the score, the greater the fear of coronavirus-19 [23].

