**Methods and analysis:**

The clinical trial is randomized in which pregnant women will be assigned equally through block randomization between two arms: (1) a control group and (2) an intervention group. The primary endpoint is the perinatal psychological distress, including perinatal depression, anxiety, and COVID-19 phobia in their third trimester; the secondary, tertiary, fourth, and fifth endpoints will be in the postnatal period (3–5 weeks, 2–4 months, 5–7 months, and 8–10 months). This trial involves pregnant women in their second trimester with no mental health illness history who communicate in English and Arabic and consent to participate. A sample size of 58 (29 participants per arm) is targeted.

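### Four of the five listed changes from baseline are visit-to-visit differences, and the baseline score is itself named a primary outcome

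*Protocol article*

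**What the plan says.** All references are to the protocol article.

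- **Primary outcomes (under Outcomes {12}).** The definition begins "The primary outcomes are baseline (T0) scores of perinatal depression, perinatal anxiety, and COVID-19-specific phobia during late pregnancy and during the follow-up" and extends to ten months after birth. As an addition to the scores it then lists "additionally computing the changes in the scores from the baseline [(T1–T0), (T2–T1), (T3–T2), (T4–T3), and (T5–T4".
- **Participant timeline {13}, Table 1 footnote.** T0 is described as "after randomization and allocation it is baseline assessment [14th week until the end of 27th" week, and Table 1 marks no intervention there. T1 "is during the 3rd trimester [28th week until the end of 42nd week] the first intervention session". T4 is a visit "in 5 to 7 months postnatal", but the Table 1 header goes from T3 to T5, and the depression, anxiety and phobia rows each carry five marks.
- **Abstract, Methods and analysis.** "The primary endpoint is the perinatal psychological distress, including perinatal depression, anxiety, and COVID-19 phobia in their third trimester". Four postnatal windows, including 5–7 months, follow as second to fifth endpoints.
- **Statistical methods for primary and secondary outcomes {20a}.** "The linear mixed-effects models will include the response variable, timepoint, randomized group, and baseline score as fixed effects". A time-by-group interaction supplies the treatment effect at each timepoint, and the model is meant for every continuous outcome.

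**The concern.** The label and the formulas cannot both be followed. A statistician who takes the label seriously computes Tk–T0; one who follows the list computes four increments between adjacent visits. These are different quantities. An increment answers whether the arms moved apart or together since the last visit. It does not answer whether the treated arm is better off than at baseline. Because the text places these changes within the primary outcomes, a report that follows the list could show null or reversed rows for the change outcomes while the treated arm was doing better throughout.

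The opening of the sentence adds a second problem. Taken literally, T0 scores are a primary outcome, yet no session has taken place at T0, so no treatment effect can exist there. It also attaches late pregnancy to T0, whereas the timeline puts T0 in weeks 14–27 and the third trimester at T1.

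**Working it through.** **Plan's own figure.** The plan gives no number for the changes. Its one computed design figure is 29 per arm (proportions 0.34 and 0.70, two-sided 5%, 80% power). The pooled-variance formula gives (1.960×√0.4992 + 0.842×√0.4344)² / 0.36² ≈ 29.0, with power 79.96% at 29 per arm. Here 29 serves only as the n of an illustration; the point does not depend on it.

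**Algebra (no SD needed).** Let δk be the expected between-arm difference in mean score at Tk, signed so that positive means benefit. Randomisation, with no session before T0, gives δ0 = 0.

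- Listed change at visit k: δk – δ(k–1)
- Change from baseline at visit k: δk – δ0 = δk

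| Effect shape | Listed differences, in order | Tk–T0, k = 1 to 5 |
|---|---|---|
| Constant d from T1 | d, 0, 0, 0, 0 | d, d, d, d, d |
| Constant d from T2 | 0, d, 0, 0, 0 | 0, d, d, d, d |
| Linear growth to d at T5 | d/5 in each | d/5, 2d/5, 3d/5, 4d/5, d |
| d at T1, waning linearly to 0 at T5 | d, –d/4, –d/4, –d/4, –d/4 | d, 3d/4, d/2, d/4, 0 |

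The second row matters because the footnote makes T1 the first session. If T1 scores are taken before that session acts, T1–T0, the one true change from baseline in the list, carries no effect. In the last row the treated arm is never worse than control, yet four listed differences point the wrong way.

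**Illustration (assumed inputs).** Assume d = 0.8 SD, correlation 0.5 between any two visits, 29 per arm, t tests, 10,000 simulated trials. Two-sided 5% rejection rates:

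| Onset | Listed differences | Tk–T0 |
|---|---|---|
| T1 | 0.85, 0.05, 0.05, 0.05, 0.05 | about 0.85 at all five |
| T2 | 0.05, 0.85, 0.05, 0.05, 0.05 | 0.05, then about 0.85 at T2 to T5 |

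With onset at T1, comparing the scores themselves gives 0.05 at T0 and about 0.85 at each of T1 to T5.

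**Range.** By the normal approximation, power for a change from T0 is Φ(d / (√(2(1–ρ)) × √(2/29)) – 1.96). For d = 0.8 and ρ = 0.5 this is Φ(3.046 – 1.96) = 0.861, close to the simulated 0.85. With d of 0.5 or 0.8 and ρ of 0.3, 0.5 or 0.7, it runs from 0.363 to 0.976; adjusting the score for T0 gives 0.514 to 0.989. The 5% at the null intervals does not change with d or ρ, since the true difference there is zero.

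**Gradual case.** If the effect grows after T1 to 0.75 SD at T5, each of the four increments is 0.75/4 = 0.1875 SD. Power is about 11% for each, against 80% for T5–T0 (ρ = 0.5).

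**T4.** The abstract, the Table 1 footnote, Primary outcomes and {20a} all call for a 5–7 month assessment. The grid has T0, T1, T2, T3 and T5: five marks for six timepoints. T4–T3 and T5–T4 need the visit that the grid lacks.

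**The case against.** A reader might infer that the trial would report no benefit at most visits even if the intervention worked. The documents do not support that. The changes are an addition; the scores in late pregnancy and follow-up are primary in the same sentence. The {20a} model adjusts for baseline and estimates the effect at each timepoint. Applied to scores, it would show a sustained effect at every visit after onset. Its references to repeated measures and to outcome data at each visit window suggest that scores are meant. The abstract puts the primary endpoint in the third trimester, and for that visit T1–T0 is a true change from baseline.

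Further points are fair. The one-interval pattern needs a constant effect. Between-visit differences are a legitimate description of when change happens, and the five listed ones sum to T5–T0, so nothing is lost from the data. The T0 wording is probably a garbled list of baseline, late pregnancy and follow-up. T0's expected between-arm difference is zero, so naming it does not cause the vanishing effect.

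What remains is this. The {20a} section covers each continuous outcome and names its dependent variable only as the response, so the listed changes qualify too. Adjusting T3–T2 for T0 does not bring back the lost contrast. The data windows in that section start at gestation week 14, so T0 could enter as both response and covariate.

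On T4, a reader might conclude that two changes cannot be computed. That follows only if Table 1 is taken literally against four other places. A column lost when the table was read cannot be wholly excluded either, although header and rows agree.

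**Conclusion.** The point holds as an error in the definition of the primary outcomes, limited to the additional change scores and the role of T0. Four of five listed differences contradict their label. Under a constant effect with arms equal at T0, exactly one of the five has a non-zero expected between-arm difference. Other shapes give d/5 increments (linear growth) or –d/4 reversals (linear waning). These results are algebra. The rejection rates are illustrative, because the effect size in SD units and the correlation are assumed. The error does not show that the mixed-model analysis of follow-up scores would miss a sustained effect.

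Naming T0 as a primary outcome, and dating it to late pregnancy, is a separate wording defect. The missing T4 column is a schedule inconsistency unrelated to the vanishing effect.

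**What to change.** 1. Define the primary outcomes as the depression, anxiety and phobia scores at the named post-baseline visits. Keep T0 only as covariate or reference, dated to the second trimester as in the timeline.
2. In {20a}, state that the response is the post-baseline score, so that T0 is not also a response.
3. Write the changes as Tk–T0 for k = 1 to 5. Alternatively, keep the listed differences but call them descriptive between-visit changes and take them out of the primary outcomes.
4. Separately, reconcile Table 1 with the 5–7 month visit in the abstract, the footnote, Primary outcomes and {20a}, so that all five places agree on whether T4 takes place.

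The cost is a few sentences and one table correction. No data are needed beyond what the outcomes section already requires, and Trial status says recruitment had not begun, so the change can be made before any outcome is seen.
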